## Abstract

**Methods::**

This randomized clinical trial was conducted at 2 reference hospitals for cancer treatment. One hundred eight women with stage I–IV breast cancer undergoing treatment (surgery, chemotherapy, radiotherapy or hormone therapy) with a partner will be included in this study. The study was authorized by the Ethics Committee of the Federal University of Ceará (Opinion number: 46,13,609) and the Maternity School Assis Chateaubriand (Opinion number: 47,42,687). Patients will be allocated to the following groups: the control group, which will not receive an active intervention, and the intervention group, which will receive 3 telenursing counseling sessions for 6 weeks. The levels of sexual function in these patients before the intervention, soon after the intervention and at 12 weeks were compared and analyzed. All data will be collected and analyzed by the JASP program.

**Results::**

Differences in levels of sexual function among women allocated to the control and intervention groups in the analyzed periods.

**Conclusion::**

This evidence-based nursing care strategy can be used to improve the sexual function of breast cancer patients and consequently their quality of life and marital relationship.

## 1. Introduction

There is a consensus in the literature that most breast cancer patients have sexual problems. These problems are due to the diagnosis or cancer treatment, including surgery, chemotherapy, radiotherapy, and hormonal therapy, which interfere directly or indirectly with sexual functioning, whether through psychological, social, or biological aspects.^[1,2]^

Changes in the sexual functioning of breast cancer patients start from treatment and may last for a long period. The younger the patient, the more severe the symptoms or sexual problems will be. These problems directly impact the quality of life of these patients and their relationships.^[3,4]^ One of the major problems surrounding this issue is the fact that many healthcare practitioners do not address the sexuality complaints of patients with breast cancer during their appointments. Therefore, most patients seek information from other sources, thus highlighting communication barriers in the professional-patient relationship and the maintenance of a taboo around sexuality and its relevance to women, especially in the context of breast cancer treatment.^[5,6]^

This problem may have been further aggravated by the pandemic context experienced in the last 2 years, especially due to the need to reduce personal interactions to minimize the risk of COVID-19 transmission. Implementing healthcare and health assessment tools that do not expose professionals or cancer patients to COVID-19 contributed to the increase in telehealth activities delivered via phone or video.^[7]^

Few studies have examined how educational interventions by phone impact the sexual function of women with breast cancer undergoing treatment,^[8–10]^ especially at the beginning of cancer treatment and led by nurses. The International Council of Nurses considers telenursing a service that enables the maintenance of effective communication with clients with chronic noncommunicable diseases, in addition to providing an effective intervention in the promotion and education for a healthy life.^[11]^

There is, therefore, a need to evaluate the impact of educational interventions performed through telenursing on the sexual functioning of women with breast cancer more deeply, aiming to guide and inform these patients about the sexual problems arising from cancer diagnosis and treatment and help them deal with these problems. This study aims to test the effect of telenursing counseling on the sexual functioning of women undergoing breast cancer treatment.

## 2. Materials and methods

### 2.1. Study design

This is a randomized clinical trial (RCT) with 2 parallel groups, with an allocation ratio of 1:1, with implementation between February 2022 and February 2023. This protocol was developed according to the guidelines of the Standard Protocol Items: Recommendations for Interventional Trials (SPIRIT)^[12]^ (Supplemental data, Supplemental Digital Content, http://links.lww.com/MD/xxx).

### 2.2. Study setting

The study will be conducted in 2 reference hospitals in the state of Ceará, Brazil. One is a university hospital linked to the Federal University of Ceará. The other is a reference center for diagnosing, treating, and monitoring cancer in Ceará.

### 2.3. Subjects

The study population will consist of women with breast cancer undergoing cancer treatment recruited using the following inclusion criteria: stage I, II, III or IV breast cancer; oncological treatment (surgery, chemotherapy, radiotherapy, or hormone therapy), as the literature indicates that all treatments interfere directly or indirectly in sexual functioning and that these effects may begin from treatment and remain for a long period;^[4,13]^ having at least one telephone number; and having a partner or spouse. The following subjects will be excluded: patients in treatment for sexual dysfunction or climacteric symptoms to reduce confounding variables in the assessment of the intervention’s outcome;^[14]^ treatment for another type of cancer; hearing impairment, as it makes communication by phone impossible; and having a medical diagnosis of any mental disorders since cognitive functioning is necessary to understand and fill in the data collection instruments.

The discontinuity criteria are patients’ withdrawal from participating in the research after the commencement of data collection, death during the study, phone change after follow-up, and not answering phone calls after 5 attempts on different dates and times. There will be no change in the participant’s allocation to minimize the risk of bias.

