### 2.7. Interventions

The control group will not receive any intervention but may receive orientations about sexuality by healthcare professionals such as social workers, nurses, psychologists, or physicians (oncologists, mastologists, or gynecologists), eventually considering that none of the institutions where the study will be undertaken has specific protocols or routines aimed at sexual and reproductive health.

Three telenursing counseling sessions will be carried out over 6 weeks in the intervention group. This period was chosen for being considerate enough to address the issues planned and to establish a bond and a relationship of trust between the researchers and the participants. Most educational interventions aimed at the sexual functioning of women with breast cancer are carried out in a period of 3 to 24 weeks.^[8,16,19,20]^ The sessions will take place at intervals of at least 15 days, considered enough for contacting all participants but not so long that would cause forgetfulness of the information provided in each contact.^[21]^

The calls will be made at times and days arranged with the participants and the researcher and are estimated to last 30 to 40 minutes. The telephone counseling will be conducted exclusively by the principal researcher to minimize the risks of divergence in the approach. The principal researcher has worked as a nurse practitioner in the public health system for approximately seven years, has a specialization degree in public health, has a master’s degree in nursing, and has worked with sexual dysfunction in women with breast cancer for 4 years.

The content of the counseling sessions will be based on the guidelines provided by the American Cancer Society for managing female sexual problems related to cancer. The contents were organized into 3 main topics: Cancer, sex, and the female body; How can treatments interfere with sexual life? And: managing female sexual problems related to cancer.^[22]^ The counseling sessions will be based on the constructs of social-cognitive theory.

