### 2.9. Outcome

The study’s primary outcome will be sexual functioning, which will be assessed using the FSFI. The FSFI is an instrument built and validated in English^[18]^ and currently has at least 20 translations in different languages. The initial validation of the FSFI obtained a Cronbach’s alpha > 0.90 and reliability coefficient in the high general retest for all domains that make up the scale (*R* = 0.79 to 0.86), demonstrating good construct validity with a statistically significant difference between the averages of groups with and without sexual desire disorder (*P* < .001). The data above support the psychometric reliability and validity of the FSFI. In 2007, the FSFI was translated and validated into Portuguese (Brazil),^[25]^ obtaining a Cronbach’s alpha of 0.92 (95% CI: 0.90–0.93) and showing adequate internal consistency. The FSFI is a self-report questionnaire composed of 19 questions to evaluate female sexual functioning, which uses a Likert scale ranging from 0 to 5 and has 6 domains: desire, subjective arousal, lubrication, orgasm, satisfaction and pain (dyspareunia).^[26,27]^

Sexual function will be analyzed at baseline (*T*0), 6 weeks after the intervention (*T*1), and 12 weeks after the intervention (*T*2). In other studies that performed an intervention to improve the sexual functioning of women with breast cancer, the outcome was evaluated between 4 weeks and 12 months after the intervention.^[8,11]^

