### 2.13. Statistical methods

The data will be compiled and analyzed in the JASP program (Copyright 2013–2021 University of Amsterdam) Version JASP 0.15.^[27]^

Descriptive statistics will be obtained for the independent variables (means for continuous variables, absolute and relative frequencies for categorical variables, and their respective confidence intervals). An ANOVA statistical test for repeated measures will be completed to assess the extent to which the control and intervention groups differ concerning the outcome variable (sexual functioning) in the periods analyzed (*T*0, *T*1, and *T*2). All statistical analyses will be performed in collaboration with external statisticians, who will not be informed about the allocation of the groups.

The dataset generated or analyzed during this study will not be publicly available due to the ethics review act. However, it will be available from the corresponding author upon reasonable request and under the Brazilian guidelines for research collaboration and data transfer.

The study results will be submitted for publication in a peer-reviewed nursing journal. No professional writer will be involved.

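### Failed phone contact ends participation, the counselling arm is more exposed to that rule, and the planned ANOVA needs all three scores, so the comparison may depart from the randomised groups

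*Protocol article*

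**What the plan says.** **Discontinuation (protocol article, 2.3).** The criteria are withdrawal, death, and "phone change after follow-up, and not answering phone calls after 5 attempts on different dates and times". The section adds: "There will be no change in the participant’s allocation to minimize the risk of bias". It does not separate stopping the counselling from stopping outcome assessment.

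**Calls by arm (2.7).** "Three telenursing counseling sessions will be carried out over 6 weeks in the intervention group", all by telephone. For the other arm, "The control group will not receive any intervention but may receive orientations about sexuality by healthcare professionals", so no counselling calls are scheduled there.

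**Outcome collection (2.9).** "Sexual function will be analyzed at baseline" (T0) and at two later times, T1 and T2. "The FSFI is a self-report questionnaire composed of 19 questions to evaluate female sexual functioning". The text shown does not say whether T1 and T2 are completed by phone or in person, and the flowchart is not shown.

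**Analysis (2.4 and 2.13).** "An ANOVA statistical test for repeated measures will be completed to assess the extent to which the control and intervention groups differ" over T0, T1 and T2. The sample size rests on the same test: 45 women per group, 90 in all, raised by 20% to 108 for losses.

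**The concern.** In this trial the telephone delivers the treatment. A rule that ends participation because calls go unanswered therefore turns non-adherence into a reason for leaving the study. It acts after randomisation, and the arm with more scheduled calls gives it more chances to act.

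The named test then completes the selection. A classical repeated-measures ANOVA needs every score, so a woman discontinued before T1 or T2 drops out of it altogether, and a T1 score from a woman who misses only T2 is discarded. Keeping her allocation unchanged preserves her arm label. It does not supply the missing score.

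At stake is whether the result estimates the effect of offering counselling to the women randomised, or compares two groups that were selected to different degrees by how easily they could be reached by phone. A later choice of model cannot recover scores that were never sought.

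**Working it through.** **1. The plan's own figure.** Inputs from 2.4: effect 0.085, read as partial eta squared; alpha 0.05; power 80%; nonsphericity correction 0.5; 2 groups; 3 times. Then f² = 0.085/0.915 and f = 0.305. With a noncentral F for the group-by-time interaction, λ = f²(N − 2)(3 − 1)(0.5). This gives N = 89, or 90 in equal arms (power 0.807), so the stated 90 reproduces, and 108 = 90 × 1.2. The point does not turn on these figures. They show that losses are covered by extra recruitment, which fits an analysis of about 90 women with complete data.

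**2. Exposure to the phone rule.**

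| How T1 and T2 are collected | Calls, counselling | Calls, control |
|---|---|---|
| In person | 3 | 0 |
| By phone | 3 + 2 = 5 | 2 |

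The difference is three calls either way.

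**3. Expected loss.** The document gives no failure rate, so the chance q that a scheduled contact fails after five attempts is an assumption. Contacts are taken as independent. Loss = 1 − (1 − q)^calls.

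| q | 5 against 2 calls | 3 against 0 calls |
|---|---|---|
| 2% | 9.6% against 4.0% | 5.9% against 0% |
| 5% | 22.6% against 9.8% | 14.3% against 0% |
| 8% | 34.1% against 15.4% | 22.1% against 0% |

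**4. Bias.** Assume that lost women, in both arms, would have improved d SD less than retained women. The mean among completers in an arm is then too high by loss × d, and the net bias is (loss in counselling − loss in control) × d.
- q = 5%, 5 against 2 calls, d = 0.5: (0.2262 − 0.0975) × 0.5 = 0.064 SD.
- The same with d = 0.3: 0.1287 × 0.3 = 0.039 SD.
- q = 5%, 3 against 0 calls, d = 0.5: 0.1426 × 0.5 = 0.071 SD.

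**5. Type I error.** Take 45 per arm, within-woman correlation 0.5, and a baseline-adjusted mean of T1 and T2. SE = √[(2/45)(0.75 − 0.25)] = 0.149. The two-sided rejection rate is Φ(−1.96 + bias/SE) + Φ(−1.96 − bias/SE).
- 0.064/0.149 = 0.43, giving 7.2%.
- 0.039/0.149 = 0.26, giving 5.8%.
- 0.071/0.149 = 0.48, giving 7.7%.
- Across q = 2% to 8% with d = 0.5: 5.4% to 9.6% for 5 against 2 calls, and 5.4% to 11.5% for 3 against 0.

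**6. Check with the planned test.** Step 5 uses a simpler contrast than the planned interaction test. The complete-case ANOVA interaction was therefore simulated under no true effect (54 per arm, correlation 0.5, 20% loss overall), with loss correlated r with change in score.

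| Loss, control / counselling | r = 0 | r = 0.3 | r = 0.5 |
|---|---|---|---|
| 20% / 20% | 0.049 | 0.051 | 0.049 |
| 11% / 29% | 0.049 | 0.062 (bias 0.06 SD) | 0.081 (bias 0.11 SD) |
| 0% / 40% | 0.049 | 0.110 (bias 0.16 SD) | 0.233 (bias 0.28 SD) |

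The unequal rows are close to what 20% overall loss implies if every scheduled call is equally likely to fail (28% against 12% for 5 against 2 calls; 40% against 0% for 3 against 0). Type I error leaves 5% only when loss is both unequal and related to outcome.

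**The case against.** **The rule applies to both arms.** This stands. If T1 and T2 are by phone, control women are lost under it too. A reader might infer that the rule hits the counselling arm alone, but the text supports only greater exposure.

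**The document does not say that discontinued women go unassessed or unanalysed.** Also true. The analysis set and missing-data handling may be in an analysis plan that is not shown, and their absence here is not a finding. What remains is a stated rule and a stated test which, followed as written, can select the arms unequally. It is therefore too strong to say that the comparison is not of the randomised groups.

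**Independence inflates the gap.** Fair. A woman who cannot be reached for a session may be equally unreachable at T1. If reachability were wholly a stable trait and T1 and T2 were by phone, both arms would lose the same share and the error would stay near 5%. This would not equalise the arms if T1 and T2 are in person.

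**The direction is assumed.** It is. A reader might infer that the bias favours counselling, but that requires women who do not answer to change less well, and nothing in the document shows it. A type I error of about 10% is also a tempting figure for the main 5% scenario. It would need 20% selective loss in counselling with none in control; with the losses in both arms counted, that scenario gives about 7%.

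**There are safeguards.** Five attempts on separate occasions, agreed call times and text reminders (2.7, 2.11) make loss less likely. Session attendance is recorded as adherence data, which could mean that a missed session is not meant to remove anyone. Read literally, the phone-change criterion falls after follow-up and would remove no one. These points argue for clearer wording in 2.3.

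**Conclusion.** The point holds as a risk that the stated rule and the stated test create together. The counselling arm has three more opportunities to meet the phone criterion, and the ANOVA leaves out any woman without all three scores. The comparison may therefore depart from the randomised groups.

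The size depends on assumptions the document cannot settle: failure rate per contact, independence of contacts, how T1 and T2 are collected, and whether lost women change differently. In the main illustration the bias is about 0.06 SD and the type I error about 7%, or about 6% with a 0.3 SD deficit. It is larger if T1 and T2 are in person and only session calls trigger the rule. It is near 5% if loss is unrelated to change in FSFI. The direction is unknown. The article's Discussion itself names retention as uncertain.

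This is a cheap improvement rather than proof of a biased trial.

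**What to change.** **Section 2.3.** State that failed phone contact or a phone change does not end outcome follow-up. State that the T1 and T2 FSFI will be sought from every randomised woman who has not died or withdrawn consent, by any available route, including the treating hospital where she was recruited. Clarify the timing meant by the phone-change criterion. When counselling calls themselves stop is a separate matter for the investigators, and nothing is proposed on it here.

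**Section 2.13.** Analyse all randomised women as allocated with a linear mixed model that uses every available FSFI score. Keep the complete-case ANOVA as a sensitivity analysis.

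The change to 2.3 matters more. A mixed model keeps the T1 score of a woman who misses only T2, but a woman lost before T1 contributes only her baseline, and the model still relies on loss being explained by the scores that were observed.

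**Cost.** Protocol wording, an extra contact number at enrolment, some tracing effort and a different model. No more patients are needed.

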### 2.4. Sample size

G*power software, Version 3.1.9.6 (German University Heinrich-Heine Universitaet, Duesseldorf)^[15]^, was used to calculate the sample size by selecting “Test F” as the family of the test, considering that the analysis of variance (ANOVA) of repeated measures with intra- and intergroup interaction will be used to verify the null hypothesis.

The sample size estimation was made using an equation based on ANOVA, which took into account an effect of 0.085 (representing an effect size of at least 0.30 in the groups) and a power of 80% in the repeated measures design (2 groups, alpha = 0.05, nonsphericity correction = 0.5). Given the parameters above, the G*power software suggested 45 participants in each group (90 participants in total). Taking into account possible sample losses, a percentage of 20% was added, which totaled a sample of 108 participants.

This effect size was stipulated by a previous study, which identified an intermediate effect size (approximately 30%) for sexual functioning among the groups (control and intervention).^[16]^ The sphericity corresponds to one of the assumptions the data must meet so that ANOVA can be used, ranging from 0.5 to 1, with 0.5 being the most rigorous.^[15]^

### 2.5. Recruitment and data collection

The patients will be approached in person at the study locations by a team of 2 researchers who will contribute to the data collection process. These researchers received a training of approximately 8 hours on the objectives and methodological procedures of the study, where simulations involving the data collection instrument were also performed. These researchers are also members of a research group that conducts research on mastectomized women at the Nursing Department of the Federal University of Ceará. After formal consent, sociodemographic and clinical data will be collected from the medical records and through the application of an adapted questionnaire.^[17]^ The questionnaire analyzes the following variables: age, education, color, marital status, length of the relationship, the average number of sexual intercourse/month, occupational status, presence of sexual problems before the diagnosis of breast cancer, city of origin, family income, religion, children, and the number of residents at home. Moreover, the following clinical data will be collected: weight, height, body mass index, menstruation status, presence of comorbidities, risk factors for breast cancer, time of diagnosis, primary tumor, lymph node and metastasis staging, previous surgery, therapeutic intervention currently implemented, and therapeutic interventions previously performed (Table 1).

**Table 1 T1:** Schedule of enrollment, interventions, and assessments.

Study period								
Timepoint	Enrolment	Allocation	Post-allocation					Close-out
	-t1	0	t1	t2	t3	t4	etc.	tx
ENROLMENT:								
Eligibility screen	X							
Informed consent	X							
*[List other procedures]*	X							
Allocation		X						
INTERVENTIONS:								
*[Counseling by telenursing]*								
*[Untreated]*								
ASSESSMENTS:								
*[List baseline variables]*	X							
*[List outcome variables]*	X					X		X
*[List other data variables]*						X		

Sexual functioning, which corresponds to the main outcome, will be analyzed using the Female Sexual Function Index (FSFI), an instrument of a specific nature and multidimensional scope that evaluates female sexual function. The scale has a possible maximum of 36 and a minimum of 2, which is obtained by summing the weighted scores of each of the 6 domains (desire, subjective arousal, orgasm, satisfaction, and pain). Higher scores reflect a better degree of sexual function^[18]^ (Fig. 1).

**Figure 1. F1:**
[figure not shown]
Flowchart of the data collection steps.

### 2.6. Allocation

Eligible participants will be randomly allocated to the intervention group or control group, with an allocation ratio of 1:1, using a simple randomization technique.^[14]^ After completion of the baseline evaluations, eligible patients will be randomized by a member of the research group that is not linked to the study. This member will assign a random numbering to each participant and then carry out a draw from the participants who will compose each group. Then, the principal researcher will carry out the intervention after being informed about the allocation of subjects in the groups.

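### Section 2.6 names simple randomisation but describes a draw of numbered participants; the procedure should be fixed as one concealed list stratified by hospital

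*Protocol article*

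**What the plan says.** All of the allocation text is in section 2.6 of the protocol article.

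- **Label.** Women are allocated "with an allocation ratio of 1:1, using a simple randomization technique".
- **Mechanism.** A member of the research group who is not linked to the study carries it out: "This member will assign a random numbering to each participant and then carry out a draw from the participants who will compose each group".
- **Timing.** "After completion of the baseline evaluations, eligible patients will be randomized". Table 1 places allocation at time 0, after enrolment.
- **After allocation.** The principal researcher learns the groups and delivers the intervention.

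Section 2.6 mentions no block, stratum or hospital. Section 2.2 states: "The study will be conducted in 2 reference hospitals in the state of Ceará, Brazil". One is a university hospital and the other a cancer reference centre; the expected number of women at each is not given. Section 2.4 arrives at 45 per group, 90 in total, after which "a percentage of 20% was added, which totaled a sample of 108 participants". Section 2.13 plans a repeated-measures ANOVA over T0, T1 and T2 and names no hospital factor.

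**The concern.** Simple randomisation means an independent assignment for each woman, like a coin toss. Arm sizes are then left to chance. A draw from a numbered set is a lottery. If a fixed number is drawn for each group, the assignments depend on one another and the arm sizes are certain. Section 2.6 uses the name of the first and wording that fits the second, so a reader cannot tell which was meant and could not repeat it.

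Two things are at stake. The first is arm size, which matters under the simple-randomisation reading. The second is hospital mix, which neither description controls. With about 54 women per arm and two hospitals of different type, the arms can differ in hospital share by chance. If FSFI changes differently over time at the two hospitals, that difference adds noise to the comparison of the arms.

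**Working it through.** **1. The planned numbers reproduce.** Inputs from section 2.4: effect 0.085 (read as partial eta squared), 2 groups, alpha 0.05, nonsphericity correction 0.5, power 80%. Three measurements come from section 2.13.

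- f² = 0.085/(1 − 0.085) = 0.0929, so f = 0.305.
- For the group-by-time interaction at N = 90: noncentrality = f² × (N − 2) × (3 − 1) × 0.5 = 0.0929 × 88 = 8.17, and power = 0.807.
- 90 × 1.2 = 108, which is 54 per group at 1:1.

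So 45 is the number per group before the allowance for losses, and 54 is the number to randomise.

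**2. What each reading gives for arm size**

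| Reading of section 2.6 | Arm sizes from 108 | Hospital balance |
|---|---|---|
| Independent assignment per woman | left to chance | left to chance |
| Draw with a fixed number per group | 54/54 with certainty | left to chance |
| Draw with no fixed number | not determined by the text | left to chance |

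**3. Simple randomisation of 108.** One arm's size is Binomial(108, 0.5), with mean 54 and SD = √(108 × 0.25) = 5.2.

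- 2.5% and 97.5% quantiles: 44 and 64.
- Chance of exactly 54/54: 7.7%.
- Chance that the arms differ by 10 or more: 38.7%.
- Chance that the smaller arm is below 45 at randomisation: 6.7%.

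**4. Power cost of unequal arms.** Take 90 evaluable women and effective N = 4 × n₁ × n₂/(n₁ + n₂). A normal approximation is scaled to 80% at 45/45.

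| Split of 90 | Effective N | Power |
|---|---|---|
| 45/45 | 90.0 | 80.0% |
| 40/50 | 88.9 | 79.5% |
| 36/54 | 4 × 36 × 54/90 = 86.4 | 78.4% |

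Under simple randomisation the 95% range for one arm of 90 is 36 to 54, so 36/54 is the edge of that range. Power averaged over all splits is 79.6%.

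**5. Hospital balance.** The split between hospitals is not given, so it is assumed to lie between 54/54 and 20/88. Within one hospital, simple randomisation gives a 95% range for one arm of 20 to 34 if it contributes 54 women, and 12 to 24 if it contributes 36. The chance that the arms differ in hospital share, by simulation over the splits 54/54, 36/72, 27/81 and 20/88, is:

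| Difference in hospital share | Simple randomisation | Draw fixed at 54/54 |
|---|---|---|
| 10 points or more | 19% to 29% | 18% to 34% |
| 20 points or more | 0.7% to 4.3% | 0.6% to 3.4% |

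Fixing the arm sizes therefore does little for hospital balance.

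**6. What that imbalance does.** The planned test compares change over time between arms. A constant FSFI difference between hospitals drops out of that comparison. A difference D between hospitals in FSFI change shifts the comparison by D × (difference in hospital share), or 0.10 × D at 10 points. The article gives no value for D. The shift averages zero over repeated randomisations, so it is a loss of precision.

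**The case against.** A fair defence has four parts.

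- **The label may be loose.** Drawing lots from a numbered list is often called simple randomisation, and the full protocol that this article condenses may give the details. Missing detail alone would be no finding. What stands is that the article states a method and then describes something that need not be that method.
- **Unequal arms hardly matter.** This is right. The average loss is 0.4 points of power (80.0 − 79.6), and it is under 2 points at the edge of the 95% range.
- **Stratification is a choice.** This is also right. Unstratified randomisation is valid, and the error rate of the test already allows for chance imbalance.
- **Safeguards exist.** Baseline is measured first, and a person not linked to the study makes the draw.

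A reader might also infer four stronger things, which the article does not support.

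- *That a draw cannot deliver the planned group size.* A fixed count delivers 54/54; the count is simply not stated.
- *That women wait in an enrolled pool and T0 goes out of date.* Section 2.6 says only that randomisation follows baseline, which also fits one-by-one or small-batch allocation. The plan also has no baseline covariate that an older T0 would weaken.
- *That the last assignments in a batch are harmfully predictable.* If everyone in the batch is already enrolled and measured, a guess cannot alter who enters or her T0.
- *That hospital goes with treatment mix or with background advice on sexuality.* Section 2.2 gives only the type of each hospital, and section 2.7 says neither institution has a specific protocol or routine in this area.

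**Conclusion.** The point holds as a request for one clear procedure and a low-cost improvement in design. It is not evidence of a biased trial.

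Section 2.6 leaves open which procedure is used, whether it runs one woman at a time or in batches, and whether group sizes are fixed. If simple randomisation is meant, one arm of 108 may fall anywhere from 44 to 64 (95% range), with a 6.7% chance of starting below 45. The price in power is small. Under either description, the chance of a 10-point or larger difference in hospital share is roughly one in five to one in three.

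The arm-size figures rest only on 108 women and equal probability. The power figures assume 90 evaluable women and a normal approximation. The hospital figures rest on assumed splits from 54/54 to 20/88. How much precision is lost through hospital imbalance cannot be computed from the article, because it gives no hospital effect on FSFI.

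**What to change.** Replace the two descriptions in section 2.6 with one procedure:

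1. Before first enrolment, the member not linked to the study prepares a computer-generated 1:1 list in permuted blocks of randomly varying size, stratified by hospital.
2. That member releases one assignment at a time, only after the woman's T0 FSFI is recorded.
3. The list and block sizes are withheld from the recruiters and from the principal researcher, who learns each assignment once it is released.
4. Section 2.13 includes hospital as a factor in the primary model, together with its interaction with time, since a difference in change is what would add noise.

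With a largest block of size b, the arms can differ by at most b/2 in each hospital, and so by at most b overall (2 × b/2). If recruitment has already begun, describe the procedure actually used and keep step 4.

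The cost is one list, made by the person already assigned to randomise, and one added factor in the model. The downside is slight predictability near the end of a block, limited by the random block sizes and by concealment from recruiters.
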